## Abstract

**Aims:**

Precision nutrition, guided by genetic testing, has emerged as a promising approach for managing obesity. However, robust clinical trials testing its effectiveness in real‐world dietary interventions remain scarce. The GenOn Programme aims to evaluate whether tailoring nutritional care based on genetic risk for obesity enhances weight loss, satiety control, and metabolic outcomes in adults with overweight and obesity.

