### Study design

2.1

The GenOn Programme is an 18‐week, 2 × 2 factorial, randomised controlled trial enrolling 120 adults of both sexes who present with overweight or obesity. The study of factors involves comparing genetic risk for obesity with nutritional interventions.

During screening visits, selected participants will be evaluated a priori for their genetic score and classified as low risk (LR) or high risk (HR) for obesity. Before intervention, participants will be randomly allocated into control or satiety intervention according to their risk classification, composing four experimental groups (control low‐risk group; control high‐risk group; intervention low‐risk group; intervention high‐risk group).

At the beginning and after 12 and 18 weeks, participants will attend the laboratory after a 10 to 12‐h fast and without water consumption, carrying 24‐h food records (three non‐consecutive days, including one weekend day) and faecal samples, to perform the study assessments. Participants will be evaluated for anthropometric and body composition analysis, questionnaire completion, blood sample collection and dietary prescription, in accordance with their assigned intervention group. Dietary interventions consist of 5 cal‐restricted nutritionally balanced plans (control intervention) or similar plans adapted to improve satiety, plus inclusion of granola (satiety intervention). All participants will receive biweekly individualised dietary counselling to promote healthier food behaviour, with emphasis on reducing the consumption of ultraprocessed foods, as recommended by Brazilian^14^, ^15^ and international^16^ guidelines. For the satiety group, granolas will be delivered, and compliance will be checked during individual counselling. Biweekly group psychological counselling, based on the experience of encounter groups, will be used to support self‐care, increase the sense of belonging to the programme and reduce dropout during the 18‐week follow‐up period. Furthermore, group counselling will be provided to address the psychological and behavioural aspects that influence the treatment of overweight and obesity, particularly among all treatment groups (Figure 1).

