### Control group

2.10

The control group will receive a balanced diet with a macronutrient distribution and a caloric restriction of 500 kcal/day. Macronutrient distributions were determined according to guidelines for the treatment of overweight and obesity, which do not account for the individual's genotype.^14^, ^15^ The menus will be divided into six meals/day (breakfast, morning snack, lunch, afternoon snack, dinner and evening snack). They will be composed exclusively of foods with a lower degree of processing (whole foods, culinary ingredients and minimally processed foods).^20^ The menus will be calculated using an Excel spreadsheet based on the Nutritional Composition Tables of Foods Consumed in Brazil.^21^ Besides, participants will be instructed to drink at least 2 L of water/day and to avoid consuming oats, seeds and cashews throughout the study period.

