### Intervention group and satiety protocol

2.11

The intervention group will receive 500 kcal/day caloric restriction and a personalised diet designed to control satiety. The distribution of macronutrients was designed based on previous studies that investigated the effect of diets with different macronutrient distributions on body weight, metabolic markers and satiety sensation in individuals carrying genetic polymorphisms in the FTO, MC4R and LEP genes.^22^, ^23^, ^24^

The menus will follow exactly the same preparation and division criteria used for the control group. In addition to calorie‐restricted meal plans, an additional protocol focused on promoting satiety (satiety protocol) will be adopted, which consists of the following strategies: high‐protein breakfast (20% of the meal's calories coming from protein), daily consumption of a standardised granola (either a sweet or a salty version), meal frequency, mastication techniques and meal duration. The protocol as a whole was developed to act on both mechanical mechanisms and hormonal signalling pathways related to satiety. All strategies adopted were based on evidence from previous studies^25^, ^26^, ^27^ that demonstrated the effect of certain nutrients and foods on the modulation of satiety, including their influence on mechanical and hormonal processes and the subjective perception of satiety.

Participants will be instructed to consume the granola sachet daily at the most appropriate time for each one, which can be divided into two portions per day. The calories of the granola will be accounted within of the calculation of the caloric‐restricted diet. Granola will be used as a strategy to provide additional fibre and monounsaturated fats, as well as to stimulate mastication. Each serving of granola consist of 30 g of oats, 24 g of seeds, 15 g of cashew nuts and 5 g of cashew oil. Two flavours of granola will be developed: (1) sweet: with an additional of 5 g of brown sugar and 10 g of black raisins and (2) salty: with an additional of 0.15 g of salt and 0.3 g of sweet paprika.

The overview of the recommendations for the control and intervention groups is presented in Table 1.

**TABLE 1 dom70414-tbl-0001:** Overview of the GenOn Programme dietary intervention.

Outcomes	Control group	Satiety group
Calorie requirement	−500 kcal/day from energy requirement^20^	−500 kcal/day from energy requirement^20^
Dietary protein intake	15%–20% of energy^14^, ^15^	20%–25% of energy^14^, ^15^

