## CONCLUSION

4

The GenOn Programme is a nutrition precision approach guided by genetic testing, which can achieve better efficacy in the treatment of overweight and obesity, demonstrating to the nutritionist and the multidisciplinary team the clinical value of genetically guided nutritional care in improving outcomes for this population.

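### The genetic score selects nobody's diet, so the pooled satiety-versus-control comparison cannot show the value of genetic guidance; only the satiety effect by risk class can, and the analysis section does not name that contrast

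*Protocol article*

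**What the plan says.** All references are to the protocol article.

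- **Aim (Abstract, Aims).** The programme "aims to evaluate whether tailoring nutritional care based on genetic risk for obesity enhances weight loss".
- **Conclusions.** Section 4 looks to demonstrate "the clinical value of genetically guided nutritional care in improving outcomes for this population". The Results and Conclusions paragraph of the abstract uses similar terms, more cautiously.
- **Allocation (2.1 Study design).** After genotyping, "participants will be randomly allocated into control or satiety intervention according to their risk classification". Participants then receive a "dietary prescription, in accordance with their assigned intervention group".
- **Use of the score (2.8 Randomisation and allocation).** Three or more risk alleles is HR and fewer than three is LR. The class is one of the minimisation factors. No other use in a participant's care is described.
- **Satiety diet (2.11).** "The intervention group will receive 500 kcal/day caloric restriction and a personalised diet designed to control satiety". Its macronutrient distribution was drawn from studies of diet effects "on body weight, metabolic markers and satiety sensation in individuals carrying genetic polymorphisms in the FTO, MC4R and LEP genes".
- **Control diet (2.10).** It follows guidelines "which do not account for the individual's genotype".
- **Table 1.** Section 2.11 states: "The overview of the recommendations for the control and intervention groups is presented in Table 1". The table has one control column and one satiety column, with no LR or HR version of either.
- **Analysis (2.28).** A mixed ANOVA takes the four experimental groups, time and genotype, with Bonferroni-adjusted post hoc comparisons. A one-way ANOVA then compares changes between control and intervention.

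**The concern.** The aim and conclusions are about a strategy: test people, then let the result shape their care. The randomised comparison is about a diet. Sections 2.10 and 2.11 blur the two. The control diet is described as ignoring genotype and the satiety diet as personalised, so satiety versus control can look like genotype-aware versus genotype-blind care. It is not, because a satiety participant with no risk alleles gets the same protocol as one with eight.

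At stake is what a positive result may be taken to mean. A satiety diet that helps everyone equally would give a favourable arm difference. In that case the genetic test adds nothing, and using it to ration the diet would cost LR people their benefit. The plan should make clear which estimate may carry a statement about genotype.

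**Working it through.** **1. Does the score change anyone's care?** Sections 2.1, 2.8, 2.10, 2.11 and Table 1, read together, say no. Diet follows the assigned arm, both arms contain LR and HR people, and neither arm's prescription is split by class. Energy is individualised in both arms (2.9), but from predicted expenditure and activity, not genotype.

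**2. What can the 2 × 2 estimate?** Let E_HR and E_LR be the extra weight loss on satiety over control in each class, and P(HR) and P(LR) the class shares.

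- Pooled arm difference = P(HR) × E_HR + P(LR) × E_LR
- Satiety-by-risk contrast = E_HR − E_LR
- Guided strategy (HR satiety, LR control) versus satiety for all = −P(LR) × E_LR
- Guided strategy versus control for all = P(HR) × E_HR

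The article gives no kilogram effects, so the following are assumed. P(HR) = 0.5 matches the planned 30 per group in four groups.

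| E_HR, E_LR (kg) | Pooled difference | Satiety-by-risk | Guided v satiety for all | Guided v control for all |
|---|---|---|---|---|
| 2, 2 | +2.0 | 0 | −1.0 | +1.0 |
| 3, 1 | +2.0 | 2 | −0.5 | +1.5 |
| 4, 0 | +2.0 | 4 | 0 | +2.0 |
| 3, −1 | +1.0 | 4 | +0.5 | +1.5 |
| −1, −1 | −1.0 | 0 | +0.5 | −0.5 |

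The first three rows share one pooled difference and differ on guidance. With P(HR) from 0.4 to 0.6, guided versus satiety for all runs from −1.2 to −0.8 kg in row 1, −0.6 to −0.4 in row 2 and +0.6 to +0.4 in row 4. No sign changes.

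Row 5 shows why one strategy comparator is not enough. Guided versus satiety for all contains no HR term. It favours guidance by 0.5 kg although guided care is 0.5 kg worse than control for all. Control for all is not enough alone either: in row 1, guidance beats it by 1.0 kg when the test contributes nothing.

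**3. Does section 2.28 name the needed contrast?** Four groups carry 4 − 1 = 3 between-subject degrees of freedom: one for diet, one for risk class and one for diet-by-risk. Genotype (LR, HR) is already one of these three, so entering it beside the four-level group factor adds nothing. The group test mixes all three. Post hoc comparison of four groups gives 4 × 3 / 2 = 6 pairs. Two of them are the satiety effect in HR and in LR. The difference between those two effects is not a pairwise comparison, and finding one significant and the other not is no test of it.

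**4. How precise would that contrast be?** Section 2.7 gives an effect size of 0.50 without stating its metric. Assume it is a standardised difference on one change score, two-sided 5%, with equal cells. With 120 analysed (30 per cell) or 84 (120 × 0.7, 21 per cell):

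- Satiety-by-risk: SE = √(4/30) = 0.365 or √(4/21) = 0.436 SD; power for 0.50 SD is about 27% or 21%.
- Satiety main effect: SE = √(2/60) = 0.183 or √(2/42) = 0.218 SD; power is about 78% or 62%.

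For 90% power the satiety-by-risk effect would have to be about 1.18 SD (120 analysed) or 1.41 SD (84). Unequal classes lower the power further: at 80:20 with 120 analysed it is 19%.

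The planned total of 120 could not be reproduced from the settings stated in section 2.7. That is a separate matter, and nothing here depends on it.

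**The case against.** The strongest reply is that this is a sound marker-stratified design. Randomisation within risk class yields all four cells, including HR on satiety and LR on control, and the mixed ANOVA over the four groups comes before the pooled comparison in section 2.28. Its post hoc comparisons can show satiety versus control in each class, and equal effects in LR and HR would be visible there. The introduction also states a narrower purpose: the effect of the satiety diet on weight in carriers of the variants.

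Most of this stands. A reader might infer that the trial holds no information on genetic targeting. The documents do not support that, because the effects in HR and LR are estimable from randomised comparisons. A reader might also infer that a diet working equally in everyone would be reported as proof of genetic guidance. No section sets that rule: nothing says the pooled difference will carry the genetic claim, and the abstract says only that findings may inform practice.

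The reply does not remove the mismatch. The aim and section 4 still speak of tailored or guided care. The contrast that bears on it is not named, and the factor list obscures it. The introduction's purpose does not close the gap either, because LR people can carry one or two risk alleles, so carriers and HR are not the same group.

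It is also fair to say that guideline care is a legitimate comparator for a guided strategy. Satiety for all should therefore not be the only benchmark, nor should control for all.

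**Conclusion.** The concern holds in this form. The stated aim and conclusions describe a test of genetically tailored care, whereas the design tests a satiety diet in two genetic risk classes. The pooled satiety-versus-control difference cannot show the value of genetic guidance. The satiety effects in HR and LR, and their difference, can inform it, but section 2.28 does not name that difference and enters genotype twice.

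The structural conclusion rests on the article's own text and needs no assumption. The kilogram figures are illustrations with assumed effects and class shares. They show that one pooled difference of 2.0 kg is compatible with guidance being 1.0 kg worse than, 0.5 kg worse than, or equal to satiety for all. The 21% to 27% power figure depends on reading 0.50 as a standardised difference on a single change score with equal cells. Randomisation, conduct and data collection are not at fault.

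**What to change.** 1. **Aim and conclusions.** In the abstract (Aims, and Results and Conclusions), the rationale at the end of the introduction, and section 4, state the question as the effect of a satiety-focused diet and whether that effect differs by genetic risk.
2. **Section 2.28.** Replace the four-group factor plus genotype with diet, risk class and time. Name the satiety-by-risk contrast on weight change as the test that carries any statement about genotype, and report it with the satiety effect in HR and in LR, each with a confidence interval. State that the pooled arm difference will not be read as evidence for genetic guidance.
3. **Only if a guided-strategy claim is wanted.** Report guided care against both comparators with confidence intervals: −P(LR) × E_LR versus satiety for all, and P(HR) × E_HR versus control for all. Require both to favour guidance, and state the class shares used. This is demanding: it needs benefit in HR and a worse result on satiety than on control in LR.

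The cost is wording, a respecified model and, for item 3, two linear contrasts on data already planned. No arm, visit or diet changes. The price is a more modest claim and wide intervals, because the trial was not sized for the interaction. The limited power should be stated beside it, so that a non-significant contrast is not taken as proof that the classes respond alike.

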**Materials and Methods:**

The GenOn Programme is an 18‐week, 2 × 2 factorial, randomised controlled trial including 120 adults classified as high or low genetic risk for obesity (variants: FTO rs9939609 and rs1121980; MC4R rs1782313; LEP rs7799039). Participants are randomised to standard or satiety‐focused dietary counselling. Both groups receive five calorie‐restricted (−500 kcal/day), nutritionally balanced meal plans. The satiety arm additionally includes a high‐protein breakfast, daily granola supplementation and behavioural strategies. Assessments at baseline, Week 12, and Week 18 include weight loss, body composition, satiety perception, quality of life, cardiometabolic markers, (epi)genetics, inflammation, neuroendocrine regulation, and metagenomics.

**Results and Conclusions:**

The GenOn Programme is a randomised controlled trial to test a precision nutrition approach for overweight and obesity, integrating genetics, dietary strategies, and behavioural support. Findings may inform dietitians and healthcare systems on the clinical value of genetically guided nutritional care to improve outcomes in the treatment of overweight and obesity.

## INTRODUCTION

1

Obesity is a chronic and progressive disease, defined by the excessive and abnormal accumulation of body fat,^1^ declared by the World Health Organization (WHO) as a global epidemic.^2^ Obesity is a multifactorial disease that is growing at alarming rates in Brazil and around the world, despite efforts to contain it. Information from the World Obesity Atlas^3^ indicates that, by 2030, 50% of adults worldwide will be living with body mass index (BMI) higher than 25.0 kg/m^2^, and 17% of men and 22% of women will be living with obesity.^3^ In Brazil, the same report also indicates that obesity affects 31% of the population, with projections indicating an increase of 33.4% among men and 46.2% among women by 2030.^3^

Obesity has a complex pathophysiological basis, characterised by dysfunction of hypertrophied mature adipocytes, imbalance in circulating concentrations of adipokines and non‐esterified fatty acids, oxidative stress and low‐grade chronic inflammatory processes.^4^, ^5^, ^6^ Furthermore, gut microbiota is considered an important factor influencing the development of obesity.^7^ Obese individuals often have microbiomes that increase energy extraction and fat accumulation.^8^ All these factors contribute to obesity‐related major complications, including type 2 diabetes mellitus (T2D), cardiovascular diseases, metabolic dysfunction‐associated steatotic liver disease (MASLD), respiratory disorders, nephropathy, musculoskeletal impairments, malignancies and psychological comorbidities.^9^

Although the obesity epidemic is associated with numerous changes in modifiable environmental factors,^10^, ^11^ the presence of genetic variants related to adiposity, food intake and metabolism can influence individual responses to the environment, as well as behaviour and food preferences.^11^ In this sense, clinical practice guidelines for the management of overweight and obesity highlight the importance of customised interventions and patient‐centred care.^12^ Precision nutrition represents an innovative approach that goes beyond conventional nutritional recommendations, providing personalised strategies based not only on phenotype but also on factors such as genetics, epigenetics, microbiome, biochemical markers, lifestyle and nutrition, which can help manage metabolic disorders such as obesity.^7^, ^13^

Unlike conventional nutritional practices, precision nutrition promotes better health outcomes by considering individual genetic variations that directly impact nutrient metabolism.^13^ In this sense, its strategy focuses on detecting individual biomarkers, allowing the application of more personalised and effective nutritional interventions to improve both prevention and treatment of obesity.^7^

The GenON Programme is a personalised nutritional intervention study conducted at the Universidade Federal de Viçosa in partnership with the Brazilian Ministry of Health, which has as its primary outcome to investigate the effect of a personalised diet that targets satiety control on body weight changes in carriers of single nucleotide polymorphisms (SNPs) in the FTO, MC4R and LEP genes. In this sense, since we believe that nutritional treatment of obesity may be more effective when the individual's genetic profile is considered, this randomised controlled trial aims to develop a genetically based personalised intervention for the nutritional care of people with overweight or obesity, representing an innovative approach to optimising the treatment of these individuals.

## MATERIALS AND METHODS

2

### Study design

2.1

The GenOn Programme is an 18‐week, 2 × 2 factorial, randomised controlled trial enrolling 120 adults of both sexes who present with overweight or obesity. The study of factors involves comparing genetic risk for obesity with nutritional interventions.

During screening visits, selected participants will be evaluated a priori for their genetic score and classified as low risk (LR) or high risk (HR) for obesity. Before intervention, participants will be randomly allocated into control or satiety intervention according to their risk classification, composing four experimental groups (control low‐risk group; control high‐risk group; intervention low‐risk group; intervention high‐risk group).

At the beginning and after 12 and 18 weeks, participants will attend the laboratory after a 10 to 12‐h fast and without water consumption, carrying 24‐h food records (three non‐consecutive days, including one weekend day) and faecal samples, to perform the study assessments. Participants will be evaluated for anthropometric and body composition analysis, questionnaire completion, blood sample collection and dietary prescription, in accordance with their assigned intervention group. Dietary interventions consist of 5 cal‐restricted nutritionally balanced plans (control intervention) or similar plans adapted to improve satiety, plus inclusion of granola (satiety intervention). All participants will receive biweekly individualised dietary counselling to promote healthier food behaviour, with emphasis on reducing the consumption of ultraprocessed foods, as recommended by Brazilian^14^, ^15^ and international^16^ guidelines. For the satiety group, granolas will be delivered, and compliance will be checked during individual counselling. Biweekly group psychological counselling, based on the experience of encounter groups, will be used to support self‐care, increase the sense of belonging to the programme and reduce dropout during the 18‐week follow‐up period. Furthermore, group counselling will be provided to address the psychological and behavioural aspects that influence the treatment of overweight and obesity, particularly among all treatment groups (Figure 1).

**FIGURE 1 dom70414-fig-0001:**
[figure not shown]
Study design of the GenOn Programme.

### Ethics statement

2.2

This study was approved by the Human Research Ethics Committee of the Federal University of Viçosa (n° 7.283.411; approval date: 11 December 2024) and by the Brazilian Registry of Clinical Trials (ReBEC) (RBR‐8csbc2g). All individuals who agree to participate in this research will provide their written informed consent prior to the commencement of data collection.

### Eligibility criteria

2.3

The study's inclusion criteria comprise: men and women aged 20–55 years who are overweight (BMI 27.0–29.9 kg/m^2^), have an elevated waist circumference (≥80 cm for women and ≥90 cm for men), and excess body fat (>30% for women and >20% for men), associated with at least one of the other components of the metabolic syndrome.^17^ Individuals with obesity (BMI ≥30 kg/m^2^) are also included if they present an elevated waist circumference and excess body fat, regardless of the other components.

The exclusion criteria are: women who are pregnant, breastfeeding, menopausal or with self‐declared intention to become pregnant during the trial; athletes; shift workers; clinical diagnosis of any mental, physical and/or intellectual disorder; food intolerances or allergies to the test products; type 1 diabetes mellitus; self‐report history of autoimmune diseases or use of immunosuppressant drugs; hormonal, digestive, inflammatory bowel, liver, kidney, pancreatic, cardiovascular or heart diseases; eating disorders; cancer; infectious episode within the past month; history of illicit drug use and/or alcohol intake >210 and >140 g of ethanol/week for men and women, respectively; planned or recent bariatric surgery; self‐reported weight fluctuations (5% of usual weight) in the past 3 months; habitual consumption of granola, nuts, whole grains or seeds (sesame, pumpkin and sunflower seeds, flaxseed) >30 g/day; adherence to vegan, vegetarian or dietary restriction diet (gluten and lactose); consumption of appetite and energy metabolism altering medications; use of vitamins, minerals and omega‐3 supplements above the Dietary Reference Intakes; use of fibre supplements (psyllium and inulin); adherence to a restrictive or therapeutic diet in the past 3 months; and current and anticipated enrolment in another research study.

